### Muscle strength

Measurements of knee extension strength representing muscle strength and handgrip strength were conducted using the Biodex System 3 Pro isokinetic dynamometer (Biodex, Inc.) and a Jamar hydraulic hand dynamometer (Performance Health, Warrenville, IL, USA), respectively. The detailed measurement was described in our previous study (13).

### Body composition

Body mass index is calculated as weight (kg) divided by height in meters squared (m^2^). ASM is defined as the total lean soft-tissue mass of four limbs. A well-trained radiological technologist measured the body composition using dual-energy X-ray absorptiometry (Hologic Horizon W, Software: Apex Versions 5.6.0.5, Hologic Inc., Marlborough, MA). The detailed measurement was described in our previous study (13).

### Biochemical measurements for outcomes

All laboratory analyses will be performed in a central laboratory. After a 12-h overnight fast, blood samples are collected at baseline and at 12 weeks to evaluate the biomarkers of muscle metabolism of IOE. The serum creatinine will be measured using modified Jaffe's kinetic alkaline picrate method. Pyruvate will be measured by the enzymatic method, and hs-CRP will be measured by latex particle-enhanced central immunoturbidimetric assay on the AU5800 chemistry analyzer (Beckman Coulter, Brea, CA, USA). An ion-selective electrode assay will measure lactate concentrations using Stat Profile pHOx Ultra analyzer (Nova Biomedical, Waltham, MA, USA).

### Dietary intake and physical activities assessments

At the baseline and after 12 weeks of the trial, participants were asked to answer a questionnaire on dietary intake and physical activities that may influence muscle strength, mass, and metabolism changes. The detailed measurement is described in our previous study (13).

### Assessments of safety and additional benefits

Safety and additional benefits are assessed at each study visit based on adverse events (AEs), vital signs, physical examination, and laboratory test results (complete blood counts, liver enzymes, glucose, and creatinine) per protocol. Reports of any other adverse events or unpredicted allergic reactions are collected throughout the study. All AEs are coded using version 21.0 of the Medical Dictionary for Regulatory Activities. We previously described the biochemical and laboratory measurements in detail (24).

## Data analyses

### Sample size determination

MedCalc version 20.113 (MedCalc Software Ltd, Ostend, Belgium) was used to calculate the sample size, based on our previous study (13). The sample size was adjusted to 40 participants per group to allow for 20% dropouts. The detailed estimation is described in our previous study (13).

### Statistical analyses

Shapiro–Wilk's test will be used for the normality distribution assessment of all variables (Table 3). A *p* < 0.05 will be considered statistically significant. Data will be analyzed using IBM SPSS Statistics 22.0 (IBM Inc., Armonk, NY, USA) and R software version 3.6.2 (http://www.r-project.org/). Intention-to-treat analysis will be primary for comparisons of outcomes between the IOE and placebo groups, with multiple imputation of missing data. Five imputed data sets will be created for missing values at the 12-week follow-up for all variables. The outcome also will be compared between the two groups using a per-protocol (PP) analysis. Intergroup comparisons of baseline characteristics will be performed using the 2-sample *t*-test or Mann-Whitney's *U*-test for continuous variables and the chi-square test or Fisher's exact test for categorical variables. ANCOVA or rank ANCOVA will be used for the primary analysis, with adjustments for the variables if there is a difference between the two groups at the start of the study and there is a difference in exercise and diet during the study period, all of which will be calculated as a delta. All randomized patients exposed to at least one dose of study intervention will be included for safety analyses, as our previous study (13).

**Table 3 T3:** Study variables.

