### Participant recruitment and screening

Study candidates are recruited through bulletin boards and social media advertisements at a tertiary hospital in Yangsan-si, South Korea. Adults aged 50–85 are screened for eligibility according to the inclusion and exclusion criteria (Table 2). This study defined relatively low skeletal muscle mass as <110% of the standard lean mass measured using the body composition analyzer (InBody 720) (13). All subjects may withdraw their consent at any time during the study. Subjects of the following criteria will be considered to have dropped out or discontinued participation in the trial and will be excluded from the per-protocol analysis: failure to take the IOE supplementation or placebo for five consecutive days, failure to attend follow-up assessments, and poor compliance (< 80%). This study protocol is similar to our previously published study (13).

**Table 2 T2:** Eligibility criteria.

**Inclusion criteria** •Aged between 50 and 85 years • Body mass index ranging from 18.5 to 30.0 kg/m^2^ • Relatively low skeletal muscle mass (< 110% of the standard lean mass measured using the body composition analyzer InBody 720) • Capable of normal physical activity
**Exclusion criteria** • Malignant tumor or severe cardiovascular diseases such as angina or myocardial infarction within the last 6 months • Any central bone fracture within the last 1 year • Uncontrolled hypertension (Blood pressure ≥ 160/100 mmHg) • Uncontrolled diabetes (fasting glucose level ≥ 160 mg/dL) • Uncontrolled hyperthyroidism or hypothyroidism • Abnormal liver function (aspartate aminotransferase or alanine aminotransferase concentration, greater than twice the upper limit of normal) • Abnormal renal function (creatinine concentration, greater than twice the upper limit of normal) • Severe gastrointestinal symptoms such as heartburn and indigestion • Those who participated in other drug clinical trials within the past 1 month • Psychiatric illnesses such as severe depression, schizophrenia, and drug addiction • Alcohol abusers • Those who are pregnant, lactating, or planning to become pregnant during the clinical trial period • Allergic reaction to the constituent foods • Those who are judged unsuitable by the researcher for other reasons

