### Outcomes

All outcomes were measured at baseline and after 12 weeks. The primary outcome measure was the change from the baseline in the peak torque (TQ) at 60°/s of knee extension/flexion representing muscle function at 12 weeks of IOE or placebo use. The secondary outcome measures were changes in appendicular skeletal mass (ASM)/height^2^ (kg/m^2^) (appendicular skeletal mass index, ASMI), ASM/weight x 100 (skeletal muscle mass index, SMI), total body fat (%), trunk body fat (%), hand grip (kg), serum creatinine, pyruvate, lactate, and high sensitivity C-reactive protein during the 12-week treatment period.

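### Five imputations are few for a primary analysis planned around 20% dropouts: inference stays valid, but a borderline verdict can depend on the random seed

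*Protocol article*

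**What the plan says.** Under Statistical analyses, the protocol article sets the primary approach: "Intention-to-treat analysis will be primary for comparisons of outcomes between the IOE and placebo groups, with multiple imputation of missing data". The next sentence fixes the number of imputations: "Five imputed data sets will be created for missing values at the 12-week follow-up for all variables". The decision rule is that p below "0.05 will be considered statistically significant", and the model is given as "ANCOVA or rank ANCOVA will be used for the primary analysis".

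Under Sample size determination: "The sample size was adjusted to 40 participants per group to allow for 20% dropouts". Under Participant recruitment and screening, dropout or discontinuation covers "failure to take the IOE supplementation or placebo for five consecutive days, failure to attend follow-up assessments, and poor compliance" (below 80%), and such participants leave the per-protocol analysis.

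Under Outcomes: "All outcomes were measured at baseline and after 12 weeks". So no intermediate outcome value is available to sharpen the imputations.

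**The concern.** Multiple imputation draws the missing values at random, so the pooled estimate and its p-value carry simulation noise that shrinks as the number of imputations, m, grows. The plan fixes m = 5 for the analysis that decides the trial, which has 80 participants and allows for a sizeable dropout rate. If the noise is large compared with the distance of the result from 0.05, the same plan run on the same data with another seed gives another verdict. What is at stake is the stability of the yes/no conclusion on the primary outcome, not its validity on average.

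**Working it through.** **Inputs from the article.** m = 5; multiple imputation in the primary analysis; 40 per group with a 20% dropout allowance; significance at 0.05; ANCOVA; outcomes at baseline and week 12 only.

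**Assumptions, because the article does not give them.** Two-sided test; a single continuous outcome; values missing at random; baseline to week-12 correlation of 0.5 and 0.8; missing share of 5%, 10% and 20%; an effect giving about 80% power with 32 evaluable per arm. By the normal approximation that effect is (1.96 + 0.842) × √(2/32) = 0.70 residual SD.

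**The plan's own figure.** The article refers the effect size, SD and power to an earlier study, so 40 per group cannot be rebuilt in full. Only the inflation step can be checked: 32 / (1 − 0.20) = 40, which is consistent with 32 evaluable per arm.

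**Analytic check.** With fraction of missing information FMI, the Monte Carlo SD of the pooled effect, in units of its standard error, is about √(FMI/m). The simulations gave FMI of about 0.21 at 20% missing and 0.10 at 10% missing.

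- 20% missing, m = 5: √(0.2/5) = 0.20
- 20% missing, m = 20: √(0.2/20) = 0.10
- 20% missing, m = 100: √(0.2/100) = 0.045
- 10% missing, m = 5: √(0.10/5) = 0.14

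Suppose that very many imputations would give z = 1.96. At m = 5 and 20% missing, 95% of seeds then fall in about 1.96 ± 1.96 × 0.20, or 1.57 to 2.35. That is p from about 0.019 to 0.12, from noise in the estimate alone.

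**Efficiency.** 1 / (1 + 0.2/5) = 0.96. The standard error grows by √1.04, about 2%.

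**Simulation.** Missing week-12 values were imputed by proper normal regression from arm and baseline. Each completed data set was analysed by ANCOVA, and results were pooled by Rubin's rules with Barnard-Rubin degrees of freedom. Each simulated trial was re-imputed with many seeds.

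Chance that two seeds disagree on p < 0.05, averaged over all simulated trials (the two values are for correlation 0.5 and 0.8):

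| Missing | m = 5 | m = 20 | m = 50 | m = 100 |
|---|---|---|---|---|
| 20% | 10.7%, 10.3% | 4.8%, 4.0% | 3.1%, 2.5% | 2.3%, 1.7% |
| 10% | 5.3%, 5.7% | 2.0%, 2.9% | 1.1%, 1.9% | 0.8%, 1.4% |

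At 5% missing and m = 5 the figure is about 3%.

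Where the noise matters, at 20% missing and m = 5. The limiting p is the value that very many imputations would give:

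| Limiting p | Central 95% of p over seeds | Seeds on the other side of 0.05 |
|---|---|---|
| 0.01 | 0.002 to 0.06 | 4-5% |
| 0.02 | 0.005 to 0.09 | about 15% |
| 0.03 | 0.009 to 0.12 | 29% |
| 0.08 | 0.03 to 0.22 | about 15% |
| 0.10 | 0.04 to 0.25 | 7% |
| 0.20 | 0.09 to 0.40 | almost none |

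With m = 100, a limiting p of 0.03 spreads only from 0.023 to 0.039, and no seed crosses 0.05.

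**Error rates.** A further simulation of 5,000 trials (effect 0.71 residual SD, correlation 0.8, 20% missing) gave type I error of 5.6% at m = 5 and 5.4% at m = 100, and power of 76% and 78%. At 10% missing, power was 83% and 84%. With no treatment effect, seeds disagreed at m = 5 in 3.6%, 2.1% and 1.6% of trials for 20%, 10% and 5% missing.

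**The case against.** The strongest reply has four parts.

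1. **Five imputations are statistically sound.** Rubin's variance already includes the extra between-imputation term, so the noise is paid for in the standard error and degrees of freedom. This stands. A reader might infer that the test is biased or its error rate inflated; the simulated type I error does not support that, and power falls by only about 1 to 3 points.

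2. **The 20% is not a missing-data rate.** A reader might take it as the expected share of missing week-12 outcomes. The article does not say so. Its definition of dropout includes missed capsules and poor compliance, and those participants can still have a torque measurement; of the listed criteria, only failure to attend follow-up by its nature leaves the outcome missing. So 20% is nearer an upper bound, which is why 5% and 10% are shown. This stands and reduces the size of the point.

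3. **Near-threshold examples exaggerate.** With a limiting p of 0.04, only about 57-58% of seeds are significant at m = 5. That describes a data set already at the boundary, not this trial's overall risk. This stands; the averages over all trials are the fair summary.

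4. **The seed belongs in the analysis plan.** A reader might infer from its absence that the sponsor could choose a favourable seed. The seed, the imputation predictors and the reporting of Monte Carlo error are ordinary analysis-plan content, so their absence from an article is no defect. A recorded seed also makes p repeatable at any m. It does not, however, make the verdict less dependent on an arbitrary draw; only a larger m does that, and m is the one item that the article itself fixes.

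**Conclusion.** The point holds as an inexpensive improvement, not as a flaw in validity. At the planning ceiling of 20% missing, five imputations leave noise of about 0.2 standard errors, and two seeds reach different verdicts in about 10-11% of trials. This falls to about 5% at 10% missing and 3% at 5% missing. The risk is concentrated where the limiting p lies between about 0.01 and 0.10; outside that range the seed rarely matters.

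The averages assume roughly 75-80% power, data missing at random and one ANCOVA-tested outcome. Changing the correlation from 0.5 to 0.8 barely moves them. The article lists knee extension and flexion, right and left, under the primary outcome, and allows rank ANCOVA and conditional adjustment. The exact percentages therefore apply to a simplified version of the primary test; the √(FMI/m) mechanism is general.

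**What to change.** In Statistical analyses, replace five with a larger prespecified number of imputations: at least 20, preferably 50-100. There is no single correct value. At 20% missing, 20 imputations bring seed disagreement to about 4%, 50 to about 3% and 100 to about 2%, so the dependence shrinks but does not vanish. Run the imputation with a seed recorded in the analysis plan before unblinding.

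The change needs no new data, no added visits and no change to the primary comparison. It costs one number in the text and some computing time.

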	**Covariables**
Demography	Age, Gender, Height (cm), Weight (kg), Body mass index (kg/m^2^), Alcohol consumption (per week, amount of alcohol at once), Smoking status (pack, years), Co-morbidities
Vital sign	Blood pressure (mmHg), Heart rate (rpm)
Additional chemistry	Free fatty acid, Creatinin kinase, Tumor necrosis factor-α, interleukin-6, Malondialdehyde, HOMA-IR
Self-Administered Questionnaires	Nutrition assessment (24-h recall method), Quality of life (EQ-5D-3L, VAS), Physical activity (IPAQ), waking log

TQ, torque; ASM, appendicular skeletal mass; ASMI, appendicular skeletal mass index; SMI, skeletal muscle mass index; HOMA-IR, Homeostatic Model Assessment for Insulin Resistance; EQ-5D-3L, Euro-QoL-5 dimensions-3 levels; VAS, visual analgue scale; IPAQ, International Physical Activity Questionnaire.

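### The primary ANCOVA chooses its covariates from observed group differences and never says that baseline torque is always included

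*Protocol article*

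**What the plan says.** The Outcomes section defines the endpoint: "The primary outcome measure was the change from the baseline in the peak torque (TQ) at 60°/s of knee extension/flexion". It also confirms that the baseline value is available: "All outcomes were measured at baseline and after 12 weeks".

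The Statistical analyses section names the model, "ANCOVA or rank ANCOVA will be used for the primary analysis", and then gives a rule for covariates in two parts:

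- The first part is a baseline trigger: "with adjustments for the variables if there is a difference between the two groups at the start of the study".
- The second is joined to it by the word *and*: "there is a difference in exercise and diet during the study period, all of which will be calculated as a delta".

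The sentence before the rule sets up baseline testing: "Intergroup comparisons of baseline characteristics will be performed using the 2-sample" t-test or its rank counterpart, with chi-square or Fisher tests for categorical items. The only threshold in the section is p < "0.05 will be considered statistically significant". The rule itself does not define what counts as a difference.

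Table 3 lists torque as the primary outcome and not among the covariables. The covariables include demography, vital signs, questionnaires and laboratory items such as "Free fatty acid, Creatinin kinase, Tumor necrosis factor-α, interleukin-6, Malondialdehyde, HOMA-IR". The Discussion in the abstract and the closing paragraph of the main Discussion both say that nutrition and physical activity will be treated as covariates.

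**The concern.** Allocation is by block randomisation (Randomization section), so a baseline difference between the arms arises by chance. A test of that difference does not show whether a variable predicts week-12 torque, which is what makes a covariate worth including. A rule built on such tests can leave out a strong predictor and admit an irrelevant one. The primary model is then unknown until the data are seen.

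The variable that matters most is baseline torque. The outcome is a change score, and no sentence says that its baseline value is always in the model. If the conditional clause governs baseline torque too, most realisations of the trial would compare raw change and give up precision that costs nothing to obtain.

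The second trigger is a separate weakness. Exercise and diet during the study are post-randomisation variables and could themselves be affected by treatment. The *and* also leaves unclear whether one trigger is enough or both are needed.

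**Working it through.** **Inputs from the article.** 40 per group, allowing for 20% dropout (Sample size determination); a threshold of 0.05, taken as two-sided; 21 covariables in Table 3 (8 demographic + 2 vital signs + 6 chemistry + 5 questionnaire items).

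**Assumed.** The baseline to week-12 torque correlation r is not in the article; 0.6 to 0.9 is used, with 0.5 as an extra case. Equal SDs at the two visits are assumed. Difference is read as p < 0.05. Only the baseline trigger is modelled, because the exercise and diet trigger cannot be quantified from the article.

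**The plan's own figure.** 32 / (1 − 0.20) = 40, so 40 per group is consistent with 32 completers per arm. The effect, SD, power and pre-dropout number are left to the earlier study, so the sample size cannot be reproduced further.

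**Step 1: how often baseline torque would enter.** Under randomisation a 5% test is positive in about 5% of trials (4.6% to 5.2% in simulation). If both triggers are required, this is an upper limit.

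**Step 2: precision.** With unit SD, Var(change) = 2(1 − r) and Var(ANCOVA) = 1 − r². The ratio is 2/(1 + r).

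| r | ratio | excess variance of raw change |
|---|---|---|
| 0.6 | 2/1.6 = 1.25 | 25% |
| 0.7 | 2/1.7 = 1.18 | 18% |
| 0.8 | 2/1.8 = 1.11 | 11% |
| 0.9 | 2/1.9 = 1.05 | 5% |

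**Step 3: power, from two anchors.**

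(a) 40 per arm, effect set so that ANCOVA always adjusted for baseline has about 80% power (8,000 simulated trials per r):

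| r | adjust only if baseline p < 0.05 | always adjust |
|---|---|---|
| 0.6 | 71.8% | 79.9% |
| 0.7 | 73.9% | 79.8% |
| 0.8 | 76.3% | 79.8% |
| 0.9 | 78.3% | 79.5% |

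(b) 32 per arm, effect set so that raw change has about 80% power (20,000 simulated trials per scenario):

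| r | never adjust | adjust only if baseline p < 0.05 | always adjust |
|---|---|---|---|
| 0.5 | 78.9% | 79.7% | 88.5% |
| 0.7 | 79.2% | 79.7% | 84.5% |
| 0.8 | 78.6% | 78.8% | 82.1% |
| 0.9 | 78.7% | 78.8% | 80.4% |

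The conditional rule recovers almost none of the available gain. At r = 0.7, fixed adjustment is worth about 4 completers per arm: 32 × (1 + 0.7)/2 = 27.2, rounded up to 28.

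**Step 4: error rate and bias.** With no treatment effect, the conditional rule rejected in 4.1% to 4.7% of simulated trials, which is slightly conservative. Given a baseline imbalance Δ, the raw change comparison is shifted by −(1 − r)Δ. At r = 0.6 and Δ = 0.3 SD the shift is 0.4 × 0.3 = 0.12 SD in size. Δ averages zero under randomisation, so the shift does too.

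**Step 5: chance entry of other covariables.** If the 21 were independent, P(at least one with p < 0.05) = 1 − 0.95²¹ = 0.66. For 10 and 20 variables the figures are 0.40 and 0.64. BMI is computed from height and weight, so independence fails and 66% is the upper end.

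**The case against.** The strongest reply is that an ANCOVA needs a covariate and that, for a change outcome, convention supplies the baseline value. Torque is absent from the covariables in Table 3, so the conditional clause may govern only the items listed there. This is a fair reading. If it is what was meant, Steps 1 to 4 fall away and only the chance selection of the other covariables remains. The text does not settle the question, which is itself the defect.

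Two further objections stand. First, r and the 80% anchor are assumptions. If the trial was sized on unadjusted change, no planned power is lost and baseline adjustment is a gain on top. Second, the simulated rule is not the whole written rule, since it leaves out the exercise and diet trigger and supplies a definition of difference.

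A reader might also infer that this rule produces false positives or a biased estimate. The article does not support that. Type I error is not inflated by the baseline trigger, and the raw change comparison is unbiased over repeated randomisations; any bias is conditional on the imbalance observed in a given trial.

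It might also be said that an article may leave such matters to the analysis plan. Here the article does not leave the matter open. It states a selection rule for the primary model, and an analysis plan that followed it would inherit the fault.

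**Conclusion.** The point holds in a limited form. The primary model is data-dependent: adjustment rests on a chance baseline difference and on post-randomisation exercise and diet, and baseline torque is not stated to be always included. The first part follows from the text alone.

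The size depends on the reading:

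- **Literal reading, difference meaning p < 0.05.** Baseline torque enters in about 5% of trials. The cost is 25% to 5% more variance, or about 8 to 2 points of power, for r from 0.6 to 0.9.
- **ANCOVA taken to imply baseline torque.** That loss disappears. What remains is up to about a 66% chance that at least one other covariable enters by chance.

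It would be tempting to say that the plan leaves baseline torque out in 95% of trials, or that the trial is underpowered. The first is one reading and not stated text. The second cannot be judged, because effect, SD and power are not in the article. The harm is moderate lost efficiency and an unfixed model, so this is a should-fix point.

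**What to change.** Replace the conditional clause in Statistical analyses with a fixed model:

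- The primary analysis is an ANCOVA of change in torque on arm plus baseline torque. Any few further baseline covariates, such as age and sex, are named in advance and included whatever the baseline comparison shows.
- Each secondary outcome uses the same form with its own baseline value.
- Baseline characteristics are reported descriptively, and baseline tests are not used to select covariates.
- Adjustment for exercise and diet during the study moves to a sensitivity analysis, labelled as post-randomisation. The statements on covariates in the abstract's Discussion and at the end of the main Discussion are aligned with this.

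The change should be made before the treatment codes are opened. No new data are needed, since the outcomes' baseline values, age and sex are already collected. The cost is a few sentences in three places, the loss of freedom to choose covariates later, and the removal of exercise and diet from the primary model. This does not settle two neighbouring matters: when rank ANCOVA replaces ANCOVA, and which of the extension/flexion and right/left torque measures is primary.

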**Discussion:**

The present study will be the first randomized, double-blind placebo-controlled trial to examine the efficacy and tolerability of IOE supplementation in adults with relatively low muscle mass. The nutritional intake and physical activity that might influence muscle strength and mass will be considered as covariates for transparency of results. The results of this study will provide clinical evidence for sarcopenia patients with nutrient treatment.

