*Ishige Okamura* (IO) is a genus of brown algae, growing attached to the rocks from Geoje Island on the southern coast to the southwest coast and all over Jeju Island, South Korea. It is also distributed and abundant throughout the coastal areas of many countries in the Northwest Pacific region (15). IO extracts (IOE) are known to have anti-obesity by inhibiting lipid accumulation and anti-diabetic effects by improving insulin resistance and protecting pancreatic β-cells dysfunction *in vitro and vivo* (16, 17). Lately, IO extract (IOE) has been reported to promote the pathway to synthesis of muscles through the myostatin/Smad3 pathway and enhance protein phosphorylation of the growth regulatory axis *in vitro* (18–20) and increase muscle mass and strength *in vivo* (21). IOE showed no significant toxicity *in vivo* or animal models (22). However, no randomized, placebo-controlled trial in humans has explored the effects and safety of IOE in adults with low muscle mass. Based on previous studies, we hypothesized that IOE improves muscle strength and function in adults. Therefore, the present study investigates whether IOE increases muscle mass and strength with regular walking compared with placebo and normal walking in middle-aged and older adults with relatively lower muscle mass.

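### The primary ANCOVA may adjust for on-study changes in exercise and diet; if IOE shifts either, the primary estimate no longer targets the total randomised effect

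*Protocol article*

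**What the plan says.** The Outcomes section defines the endpoint: "The primary outcome measure was the change from the baseline in the peak torque (TQ) at 60°/s of knee extension/flexion", at 12 weeks. The Statistical analyses section makes intention-to-treat primary, with multiple imputation, and then gives the model: "ANCOVA or rank ANCOVA will be used for the primary analysis, with adjustments for the variables if there is a difference between the two groups". That first condition concerns baseline imbalance. The same sentence then adds a second condition, on behaviour after baseline: "and there is a difference in exercise and diet during the study period, all of which will be calculated as a delta".

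The section on dietary intake and physical activities gives the timing: "At the baseline and after 12 weeks of the trial, participants were asked to answer a questionnaire on dietary intake and physical activities". Table 1 schedules the walking log at visits 2, 3 and 4. Table 3 lists the activity instruments as "Physical activity (IPAQ), waking log", next to a 24-hour dietary recall.

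The abstract and the Discussion both state: "The nutritional intake and physical activity that might influence muscle strength and mass will be considered as covariates for transparency of results". The article describes no primary model without the on-study terms.

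**The concern.** A change in exercise or diet from baseline to week 12 is a post-randomisation variable. In a blinded trial, an arm difference in it is either chance or a consequence of treatment. If it is a consequence, two things follow:

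- Any benefit that IOE brings through greater activity is adjusted away.
- If something unmeasured, such as general health or motivation, drives both activity and torque, conditioning on activity links treatment to that factor and biases the contrast, even when IOE has no effect on torque.

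The article itself gives one link of this chain: it collects diet and activity because they may influence muscle strength, mass and metabolism. Whether IOE changes human activity or diet is unknown.

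At stake is the only primary model described. An intention-to-treat comparison is normally read as the total effect of being assigned IOE. Under this rule, the quantity estimated depends on what participants did after randomisation and on whether a difference happened to be detected.

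**Working it through.** **Plan's own figure.** The article gives 40 per group after a 20% dropout allowance. 32/(1 - 0.20) = 40, so this fits 32 evaluable per arm. No effect size, SD or power is stated, so the calculation cannot be reproduced further. The point does not depend on it.

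**Inputs.** From the article: 40 per arm, significance at p<0.05 (two-sided assumed), and ANCOVA with on-study deltas entered if a difference is found. Assumed, because the article gives none of these: unit within-arm SDs; shift *a* of IOE on activity, 0 to 0.8 SD; loading *u* of one unmeasured factor on both activity and torque change, 0.3 to 0.5; effect *b* of activity on torque, 0 or 0.4; trigger, a t-test on the activity delta at p<0.05.

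**Step 1: always adjusting (closed form, as an outer reference).** The within-arm slope of torque on activity is b + u². The adjusted contrast is the total effect minus a(b + u²).

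- True effect zero, a = 0.5, u = 0.5: 0 - 0.5 × 0.25 = -0.125.
- Same with u = 0.3: 0 - 0.5 × 0.09 = -0.045.
- Effect wholly through activity, a = 0.5, b = 0.4, total 0.5 × 0.4 = +0.20. With u = 0.5: 0.20 - 0.5 × 0.65 = -0.125. With u = 0.3: 0.20 - 0.5 × 0.49 = -0.045.

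**Step 2: the conditional rule as written (simulation, 40 per arm).** Activity enters only if the trigger fires; otherwise the model adjusts for baseline only. Repeat runs move the averages by about 0.01.

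| True effect on torque | Activity shift | Average estimate, u from 0.3 to 0.5 |
|---|---|---|
| 0 | 0 | about 0 |
| 0 | 0.2 | -0.01 to -0.02 |
| 0 | 0.5 | -0.04 to -0.09 |
| 0 | 0.8 | -0.07 to -0.19 |
| +0.20, all through activity | 0.5 | +0.02 to -0.05 |

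Across the zero-effect rows, type I error is about 4% to 13%; the lower end is simulation noise around 5%. At u = 0.5 it is about 7% for a shift of 0.5 and 13% for 0.8.

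**Step 3: why the trigger does not protect.** With no shift it fires in about 5% of trials. At 40 per arm and u = 0.5 it fires in 60% for a shift of 0.5 and 94% for 0.8. For the 0.5 case with true effect zero, the adjusted estimate averages -0.120 in the triggered 59.8% of trials. The remaining trials average (0.007 - 0.598 × 0.043)/0.402 = -0.047 under the baseline-only model, because selecting trials with little observed activity difference also selects on the unmeasured factor. Together: 0.598 × (-0.120) + 0.402 × (-0.047) = -0.091.

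**Step 4: no unmeasured factor is needed for attenuation.** With u = 0, a = 0.5, b = 0.4 and a direct effect of 0.50, the total is 0.50 + 0.20 = 0.70. At 40 per arm the conditional rule averages 0.55, and rejection falls from 87% to 69%.

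**Step 5: direction.** With a shift of -0.5 and u = 0.5, the bias under the conditional rule is about +0.10, in favour of IOE.

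**Step 6: after the fix.** Adjusting for baseline only recovers the total effect in every scenario, within simulation error, with type I error of about 5%.

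**The case against.** **Purpose.** The authors know that diet and activity affect strength, and the Background frames the question as "whether IOE increases muscle mass and strength with regular walking compared with placebo and normal walking". They probably meant to remove chance behavioural imbalance. That explains the choice but does not support it: no estimand holding walking or diet fixed is defined, and primary intention-to-treat points to the total effect.

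**Size.** Nothing in the article says that IOE moves activity by 0.5 SD. At a shift of 0.2 the bias is at most about 0.02, and at zero there is none. This stands, and is why the result is given as a range.

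**Wording.** The sentence is loose. It could require both a baseline and an on-study difference, in which case adjustment is rarer and the average bias smaller than shown. The delta could also refer to the outcomes. On any reading, post-randomisation exercise and diet either enter the primary model or decide its form.

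A reader might infer more than the article supports:

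- *That the model always adjusts.* It adjusts only if a difference is seen, so the -0.125 figures in Step 1 are not the planned analysis.
- *That the inflated error means false claims of benefit.* For positive activity shifts the excess rejections mainly favour placebo; only a negative shift reverses this.
- *That the Table 3 biomarkers enter the model too.* "Free fatty acid, Creatinin kinase, Tumor necrosis factor-α, interleukin-6, Malondialdehyde, HOMA-IR" appears under Covariables, but that block also holds vital signs and quality of life. The analysis text names only exercise and diet as on-study adjusters and never says that week-12 biomarker values are used.
- *That the statement in the abstract and Discussion proves post-randomisation adjustment.* It gives no timing and is compatible with baseline values. The evidence is the clause in Statistical analyses.

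**Conclusion.** The point holds in conditional form. The stated primary analysis may condition on behaviour measured after randomisation, and if IOE changes that behaviour, the estimate departs from the total randomised effect, in either direction. Under the assumed inputs, the distortion is negligible for a shift of 0.2 SD or less when the true effect is zero. It reaches about -0.19 SD, with type I error near 13%, at a shift of 0.8 and loading of 0.5. A +0.20 SD benefit carried wholly by activity is largely or entirely lost at a shift of 0.5. All these sizes rest on assumed shifts, loadings and trigger, none of which the article supplies.

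It would go too far to say that the estimate necessarily fails to measure the randomised effect: if IOE leaves diet and activity alone, there is no material bias. It still needs correcting, because this is the sole primary model described and the rule acts most often in the case where it does harm.

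**What to change.** Delete on-study exercise and diet deltas from the primary model, both as covariates and as a trigger. Adjust only for baseline values named in advance: baseline torque, with baseline IPAQ and baseline intake if wanted. Report on-study activity and diet by arm as descriptive results. Any model adjusted for their deltas can stay as a labelled exploratory or sensitivity analysis, with a note that it does not estimate the total effect of assignment to IOE.

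The cost is wording in the protocol and analysis plan. No data collection, visit or sample size changes, and no analysis is lost.
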